## Methods and design

### Study aims, research questions and outcomes

The primary aim of MERIT is to assess the effectiveness of daily use of D-mannose compared with placebo in preventing symptomatic UTI in women.

The primary outcome of the trial will be the proportion of women experiencing at least one further episode of clinically suspected UTI for which they contact ambulatory care (out of hours primary care, in hours primary care, ambulance or the emergency department) within 6 months of study entry.

Secondary outcomes will include (within 6 months of study entry):

Number of days of moderately bad (or worse) symptoms of UTI.Time to next consultation with a clinically suspected UTI.Number of clinically suspected UTIs.Number of microbiologically proven UTIs.Number of antibiotic courses for UTI.Report of consumption of antibiotics using diary during periods of infection.Proportion of women with a resistant uropathogen culture during an episode of acute infection.Hospital admissions related to UTI.Quality of life and healthcare utilisation related to UTI.Healthcare utilisation recorded in the participant diary and during a notes review.Acceptability and process evaluation conducted via telephone interviews (after 6 months).

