### Sample size considerations

A recent study to evaluate prophylactic treatment for RUTI in a similar population^20^ found that 26.6% of women in the control arm experienced an RUTI within 6 months. Our patient and public involvement advisors suggested that in order to commit to daily use of a prophylactic regime, they would require evidence of at least a 50% reduction in the chance of a further UTI during the period of prophylaxis. To detect this reduction with a two-sided Fisher’s exact test with 90% power and an alpha of 0.05 we would require 203 participants in each arm. This equates to 508 participants if a 20% loss to follow-up is assumed. This sample size is also adequate to power the key secondary outcome (the number of RUTI’s experienced over 6 months), and detect a relative incidence rate of 0.5 between the treatment and placebo groups, assuming a base rate of 0.36 as estimated by Maki *et al*.^20^ If the estimated percentage of participants who have either withdrawn or failed to respond to any study team communication for an extended period seems likely to rise above the 20% initially allowed for, we will recruit additional participants, up to a maximum of 598 participants.

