### Statistical analysis

The primary outcome, the proportion of women experiencing at least one further episode of UTI symptoms for which they visited their GP within 6 months of study entry, and other binary outcomes, will be analysed on an intention-to-treat basis by means of a generalised linear mixed effects model with binomial distribution and log link function, including a random effect for practice and fixed effect for randomisation group. Therefore, treatment groups will be compared on the basis of an adjusted risk ratio. The number of days of moderately bad symptoms of UTI, the number of UTI’s experienced in 6 months, and number of antibiotic courses for UTI in 6 months, will be analysed by means of a generalised linear mixed effects model using the Poisson distribution and log link function, including a random effect for practice and a fixed effect for randomised group. Defined daily ooses (DDDs) will be analysed by means of a linear mixed-effects model including a random effect for practice and fixed effects for randomised group and baseline DDD, treating this outcome as continuous. We will analyse the overall DDD as well as the individual antibiotic DDDs.

The amount of missing primary outcome data is expected to be very low as it is collected via notes review. The model chosen to analyse the primary outcome implicitly accounts for data missing at random, however, the data missing mechanism will be explored. Summary statistics will be presented for baseline covariates of those participants who completed and those who were lost to follow-up for the primary outcome. Baseline covariates associated with missingness will be identified by analysing each baseline covariate in a logistic regression model to determine which (if any) are associated with missingness of the primary outcome. The associated p value will be reported alongside the summary statistics. Any baseline factors found to be associated with missingness of the primary outcome will be included in a sensitivity analysis.

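### The primary model is a complete-case analysis, so the unqualified missing-at-random claim is too broad, and univariable screening for missingness is a weak way to choose the sensitivity covariates

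*Protocol article*

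**What the plan says.** The protocol article, under Study aims, research questions and outcomes, defines the primary outcome as "the proportion of women experiencing at least one further episode of clinically suspected UTI for which they contact ambulatory care" within 6 months. That is one binary value per woman. Under Statistical analysis the model is a generalised linear mixed model with "binomial distribution and log link function, including a random effect for practice and fixed effect for randomisation group". No baseline covariate is listed.

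The same section says: "The amount of missing primary outcome data is expected to be very low as it is collected via notes review". It then asserts: "The model chosen to analyse the primary outcome implicitly accounts for data missing at random". That sentence goes on to say that the missingness mechanism will be explored. Women with and without the primary outcome are to be compared at baseline, and "Baseline covariates associated with missingness will be identified by analysing each baseline covariate in a logistic regression model". Finally: "Any baseline factors found to be associated with missingness of the primary outcome will be included in a sensitivity analysis".

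Box 1 (Baseline assessment) shows that age, contraceptive and hormonal treatment, and UTI episodes in the previous 12 months are collected before randomisation.

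**The concern.** A likelihood analysis is protected against missing-at-random data only for missingness that depends on what the model conditions on. In a longitudinal model this includes earlier outcomes; in a covariate-adjusted model it includes the covariates. This model has neither. Its protection extends to arm and practice and no further, yet the sentence carries no such limit. A reader could take the primary result as robust to missingness driven by UTI history or age.

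The fallback has three weaknesses. It chooses covariates by a test of association with missingness, which has little power when few outcomes are missing. No arm term or interaction is described, so effects on missingness that run in opposite directions by arm can cancel. And it does not ask whether a covariate predicts outcome, which is needed before adjustment for it can remove bias. At low missingness the sensitivity analysis may often adjust for nothing and simply repeat the primary one.

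**Working it through.** **Inputs from the protocol article.** Control risk 26.6%, 50% relative reduction, 203 per arm, 508 in total, 20% loss to follow-up (Sample size considerations); the model and the missing-data text (Statistical analysis). No percentage of missing primary outcomes is given beyond the expectation that it will be very low. The missingness rates, covariate prevalence, covariate effects and p<0.05 threshold used below are therefore assumptions.

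**The plan's own figure.** For 26.6% against 13.3%, the continuity-corrected formula gives 203 per arm, and the exact power of the two-sided Fisher test at 203 is 90.5%. Then 406/0.8 = 507.5, rounded up to 508. The sample size reproduces and is unaffected by this point.

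**Step 1: what the model does with a missing outcome.** Given her practice effect, a woman contributes μ if she has the event and 1−μ if not. If her outcome is missing, the likelihood sums over both: μ + (1−μ) = 1. She contributes a factor of one. As a numerical check, the stated model was fitted to 500 simulated women in 50 practices with about 10% missing, once summing over the unobserved outcomes and once dropping those women. Both fits gave log risk ratio −0.71499 (risk ratio 0.489) and negative log-likelihood 221.847. The model is the complete-case fit.

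**Step 2: size of the bias.** Take a binary covariate X with 50% prevalence that doubles or triples risk, control risk 26.6%, and a true risk ratio of 0.50 at both levels of X. Practice variation is set aside. The expected complete-case risk in an arm is Σ(1−mₓ)pₓ / Σ(1−mₓ), where mₓ is the proportion missing at level x.

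Worked case: X doubles risk, so p₀ = 0.266×2/3 = 0.1773 and p₁ = 0.3547. Loss at X=0/X=1 is 10%/30% in placebo and 30%/10% in D-mannose.
- Placebo: (0.9×0.1773 + 0.7×0.3547)/1.6 = 0.255
- D-mannose: 0.5×(0.7×0.1773 + 0.9×0.3547)/1.6 = 0.1385
- Ratio: 0.544

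| Missing | Pattern (placebo; D-mannose) | Risk ratio, X doubles / triples risk |
|---|---|---|
| 20% | 10/30; 10/30 (same in both arms) | 0.500 / 0.500 |
| 2% | 1/3; 2/2 (placebo only) | 0.502 / 0.503 |
| 2% | 1/3; 3/1 (opposed) | 0.503 / 0.505 |
| 5% | 2.5/7.5; 7.5/2.5 (opposed) | 0.509 / 0.513 |
| 20% | 10/30; 20/20 (placebo only) | 0.522 / 0.533 |
| 20% | 10/30; 30/10 (opposed) | 0.544 / 0.567 |

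When dependence on X is the same in both arms, the ratio is unbiased, although the control risk falls to 25.5% or 24.9% at 20% missing. The mirror image of the opposed pattern moves the ratio the other way: for doubled risk, 0.127/0.277 = 0.46.

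**Step 3: power of the screen.** There are 508 women, 254 at each level of X. For odds ratio 2 at 2% missing (about 10 women), the two levels lose 1.35% and 2.65%. The Wald standard error of the log odds ratio is √(1/3.43 + 1/250.6 + 1/6.73 + 1/247.3) = 0.67. Then ln 2/0.67 = 1.035, and power is Φ(1.035 − 1.96) ≈ 18%. At 5% missing (about 25 women), the same formula gives 37%. Simulated likelihood-ratio tests give:

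| Missing | Odds ratio 2 | Odds ratio 3 |
|---|---|---|
| 1% | 17% | 28% |
| 2% | 22% | 41% |
| 5% | 39% | 73% |
| 10% | 64% | 95% |
| 20% | 87% | >99% |

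**Step 4: what pooling the arms hides.** In the opposed 20% pattern, each level of X loses (10%+30%)/2 = 20% over both arms. The pooled odds ratio is 1, so the screen would flag X only at its false-positive rate, even though this is the most biased row of the Step 2 table.

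**The case against.** The strongest reply is that the sentence is loose rather than false. The model is valid under missing at random given arm and practice, and the text goes straight on to an exploration of missingness and a sensitivity analysis. That is fair, and it limits the criticism to the missing qualifier and the choice of fallback.

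The two harms also belong to different situations. The screen is weak at 2–5% missing, where bias is negligible or small. Bias is visible at 20%, where the screen has good power for a covariate acting alike in both arms. This stands, except that such a covariate leaves the risk ratio unbiased in Step 2, while the opposed pattern that biases it most is hidden by pooling.

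Three stronger readings are tempting, and the document does not support them.
- **That the screen cannot find relevant covariates.** It can: 87% power for an odds ratio of 2 at 20% missing.
- **That a fifth of primary outcomes will be missing.** Sample size considerations does inflate 406 to 508 for 20% loss, but describes the monitored group as women who withdraw or stop responding. The outcome comes from notes review, so many of them could still have one.
- **That a null effect would appear as a sizeable one.** With risks of 40% and 13.2% in two equal strata and 20% loss in the opposed pattern, a true ratio of 1.00 does become 0.283/0.249 = 1.13. But this needs odds ratios for missingness of 3.9 in one arm and 1/3.9 in the other, an interaction of about 15, in a double-blind trial. The same pattern at 2% loss gives about 1.01.

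Imputation details and ranges for data missing not at random may properly sit in an analysis plan that is not shown. Their absence here is not criticised.

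**Conclusion.** The point holds in a limited form. With one binary outcome per woman and only arm and practice in the model, the primary analysis is complete-case. The missing-at-random statement is correct only for missingness that depends on arm and practice. This follows from the model as written and needs no assumed figures.

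The screen is a poor basis for selecting sensitivity covariates when few outcomes are missing, is blind to opposed effects by arm, and ignores prediction of outcome. The power figures rest on the assumed 50% prevalence, odds ratios and p<0.05 threshold.

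The consequence for the result is modest. At the very low missingness the plan expects, bias in the risk ratio is negligible. It becomes material only if loss is large and its dependence on outcome predictors differs by arm, and nothing in the document shows that this is likely. The screen feeds only a sensitivity analysis, so the primary estimate does not change.

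**What to change.** Replace the missing-at-random sentence with a statement that the primary analysis uses women with an observed outcome and is valid under missing at random given arm and practice.

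Fix the sensitivity analysis in advance. Either adjust the primary model for baseline predictors of outcome or impute by arm using them, whatever their p-value for missingness. Suitable candidates already collected are UTI episodes in the previous 12 months, age and hormonal treatment. Imputing by arm also allows for covariate effects on missingness that differ between arms. The logistic models for missingness can stay as description.

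The cost is a change of wording, slightly more analysis work on data already collected, and a more modest robustness claim. The sample size and the primary estimate are unchanged.

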### Data management

Data management will be performed in accordance with Primary Care Clinical Trials Unit Data Management standard operating procedures. Study-specific procedures will be outlined in a Data Management Plan to ensure that high quality data are produced for statistical analysis.

### Potential risks

It is anticipated that the potential risks of this study are low and similar to those attributable to usual care.

### Health economic evaluation

A cost effectiveness analysis from a health system perspective with a time horizon of 6 months will be conducted alongside this study. The primary outcome measure for the cost utility analysis will be the quality adjusted life years (QALYs). Data collection to facilitate analysis includes resource use and health outcomes. Data from the participant diary and electronic medical record review will be the main source of resource use. Unit costs associated with resource use items will be obtained from national standards. Health outcomes will be measured using the 5-level version of the EuroQol 5-dimensional questionnaire (EQ-5D-5L).

Data analysis will be conducted on an intention-to-treat basis using an incremental approach. Resource use and unit cost will be combined to calculate healthcare costs for each participant and mean cost for each study arm. EQ-5D-5L utility values will be calculated using the UK-based algorithm. Using the under the curve methods to combine utility values and associated time durations will produce QALYs for each participant and mean QALYs for each study arm during the 6-month study period. Mean differences in costs and QALYs between the study arms will be estimated as incremental cost per QALY gained. Given the fact that antibiotics are currently the mainstay treatment for both acute and RUTIs, the issue of how the cost of antibiotic resistance should be incorporated into economic evaluation will be explored in the analysis.

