### Baseline assessment

Participants will have a baseline assessment (either in person with their GP or research nurse online, or by telephone with a member of the research team). During the baseline assessment the study will be explained, informed consent (see online supplemental file 1) will be obtained and data will be collected (see box 1). Participants will also be asked to send in a urine sample (when they are asymptomatic of a UTI) at baseline and have the option to also send in a perineal swab sample.

10.1136/bmjopen-2020-037128.supp1Supplementary data

Box 1Data collection throughout the trialBaseline:1. Demographic questions: including age.2. Medical history (by patients).3. Use of contraceptives and hormonal treatment.4. Urinary tract infection (UTI) episodes in the last 12 months.5. EuroQol 5-dimensional questionnaire (EQ-5D-5L).Weekly contact/monthly contact:1. UTI episodes in last week/month, respectively.Daily UTI diary1. UTI symptoms.2. UTI treatment.3. EQ-5D-5L.Six month questionnaire1. UTI episodes in the last month.2. EQ-5D-5L.Notes review and urine culture result1. Recorded UTIs during the study period.2. Healthcare contact for UTIs recorded.3. Antibiotics given for UTIs recorded.4. Culture results for UTIs recorded.5. Unscheduled hospital admissions.

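### The economic section names no adjustment for baseline EQ-5D-5L in the QALY comparison; under stated assumptions this makes the variance about 2/(1 − rho) times what it need be

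*Protocol article*

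**What the plan says.** The Health economic evaluation section makes QALYs the main outcome of the cost-utility analysis, over a 6-month horizon ("A cost effectiveness analysis from a health system perspective with a time horizon of 6 months will be conducted alongside this study"). Utilities are combined by area under the curve into a QALY for each participant and a mean for each arm. The comparison follows: "Mean differences in costs and QALYs between the study arms will be estimated as incremental cost per QALY gained". No covariate is mentioned.

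Box 1, under Baseline assessment, lists the "EuroQol 5-dimensional questionnaire (EQ-5D-5L") among the baseline items. It lists the instrument again in the daily UTI diary and in the 6-month questionnaire, but not at the weekly or monthly contacts.

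The Statistical analysis section does name a baseline covariate for one continuous outcome, the antibiotic defined daily doses: "fixed effects for randomised group and baseline DDD".

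**The concern.** Baseline utility is measured before treatment can act, yet it forms part of each woman's QALY. A chance difference between arms at baseline therefore enters the incremental QALY in two ways. One is mechanical, because baseline is a point under the curve. The other runs through its correlation with later utility. A difference in arm means leaves both in place; regression on baseline utility removes them.

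The incremental QALY is the denominator of the cost-effectiveness ratio, and preventing a modest number of short episodes can only produce a small QALY difference. Noise in that quantity carries directly into the ratio and its uncertainty.

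**Working it through.** **The plan's own figure.** The article states no SD, correlation or power for QALYs. Its only sample size is for the primary outcome: "found that 26.6% of women in the control arm experienced an RUTI within 6 months", with a target of half that, 0.133. A continuity-corrected two-proportion calculation gives 203 per arm, and exact Fisher power at 203 per arm is 0.905. This agrees with "with 90% power and an alpha of 0.05 we would require 203 participants in each arm". Then 406/0.8 = 507.5, rounded up to the stated 508. This has no bearing on the QALY issue beyond supplying 203 per arm for illustration.

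**Inputs not in the article (assumed).** Rho 0 to 0.7; utility SD 0.10 to 0.25; equal SDs at baseline and 6 months unless varied below.

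**Step 1: the two-point curve.** Over half a year, the trapezoid is Q = 0.5 × (u0 + u6)/2 = 0.25(u0 + u6).

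**Step 2: effect of a chance baseline difference d.** The expected shift in the unadjusted QALY difference is 0.25d + 0.25·rho·d = 0.25(1 + rho)d. That is 0.25d at rho = 0 and 0.425d at rho = 0.7.

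**Step 3: variance ratio.** Unadjusted variance is proportional to 2(1 + rho), and baseline-adjusted variance to 1 − rho². The ratio is 2(1 + rho)/(1 − rho²) = 2/(1 − rho).

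| rho | unadjusted/adjusted variance | SE ratio | simulated variance ratio |
|---|---|---|---|
| 0 | 2.0 | 1.41 | 1.9 |
| 0.3 | 2.9 | 1.69 | 2.8 |
| 0.5 | 4.0 | 2.00 | 4.2 |
| 0.7 | 6.7 | 2.58 | 6.4 |

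The simulation used 4,000 runs with 203 per arm. Both estimators centred on zero.

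**Step 4: absolute size at 203 per arm.** With SD 0.2 and rho 0.5, and √(2/203) = 0.0993:
- Unadjusted SE = 0.25 × 0.2 × √3 × 0.0993 = 0.0086.
- Adjusted SE = 0.25 × 0.2 × √0.75 × 0.0993 = 0.0043.
- A one-SE baseline imbalance is 0.2 × 0.0993 = 0.020, and it shifts the unadjusted difference by 0.375 × 0.020 = 0.0074. Across SD 0.10 to 0.25 and rho 0.3 to 0.7 the shift is 0.003 to 0.011.

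For scale, the sample size section plans for a rate ratio of 0.5 on a base of 0.36 UTIs, so 0.18 averted per woman. At an assumed 5 to 10 days and a utility loss of 0.2 to 0.4 per episode, the direct gain is 0.18 × (5 × 0.2)/365 = 0.0005 to 0.18 × (10 × 0.4)/365 = 0.002 QALY.

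**Step 5: diary values.** Let f be the variance of the diary loss divided by Var(0.25u), with the loss independent of baseline. The ratio becomes (2(1 + rho) + f)/((1 − rho²) + f). With Poisson counts at 0.36 per woman, f = 0.36 × (days × loss/365)²/(0.0625 × SD²).

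| Episode (assumed) | SD | f | variance ratio, rho 0 to 0.7 |
|---|---|---|---|
| 7 days, loss 0.3 | 0.2 | 0.005 | 2.0 to 6.6 |
| 7 days, loss 0.3 | 0.1 | 0.02 | 2.0 to 6.5 |
| 14 days, loss 0.4 | 0.2 | 0.03 | 2.0 to 6.3 |
| 14 days, loss 0.4 | 0.1 | 0.14 | 1.9 to 5.5 |

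Much larger diary variance would lower the ratio: 1.5 to 2.9 at f = 1, and 1.3 to 2.2 at f = 2.

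**Step 6: unequal SDs.** With a 6-month SD 1.5 times baseline, the ratio over the same rho range is 1.4 to 4.7. With 0.75 times, it is 2.8 to 9.1.

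**The case against.** **The article never calls the comparison raw or unadjusted.** A regression coefficient for arm is also an estimated mean difference, and a condensed article may leave covariates to a fuller protocol or health economics plan. This stands in part. A reader might infer that the team has decided against adjustment, or take the baseline term for defined daily doses as proof of such a decision; the text supports neither. What it does show is a described chain from utilities to arm means to their difference, with no baseline term, in an article that names one elsewhere. If a fuller plan already adjusts, only this wording needs aligning.

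**The curve is not strictly two-point.** The diary adds EQ-5D-5L values during UTIs, which is true and can reduce the gain. But the Follow-up section asks for the diary only when a woman has a UTI. On the planning figure of 26.6%, about 73% of controls would contribute none. At 0.36 episodes per woman, f stays well below 1 in the cases tried. The eligibility criteria admit women with two UTIs in 6 months. At that rate, with 14-day episodes, a loss of 0.4 and SD 0.1, f = 0.136 × 2/0.36 = 0.75 and the ratio is 1.6 to 3.3. So the reduction can be real, but a gain remains.

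**Randomisation makes the unadjusted difference unbiased, and its SE already includes baseline imbalance.** This stands in full. The 0.0074 shift is smaller than the 0.0086 unadjusted SE. The issue is precision and conditional imbalance, not validity.

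**A tempting stronger reading concerns the decision.** One might set the Background's price of at least £25 a month against a cost-per-QALY threshold and conclude that baseline imbalance could overturn the adoption decision. The documents do not support this. That figure is what women pay, the evaluation takes a health-system perspective, and no threshold is given. The adjusted 95% half-width, 1.96 × 0.0043 = 0.0084, would still leave wide uncertainty.

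**Conclusion.** The point holds as one of efficiency. As worded, the incremental QALY is a difference in arm means with no term for baseline utility, although that value is collected and forms part of the outcome. The variance is about 2/(1 − rho) times that of the adjusted estimate: roughly 2 to 7 times for rho 0 to 0.7. This rests on an approximately two-point curve and equal SDs. The SDs and rho are assumptions, since the article gives none. The multiple is smaller if UTI losses unrelated to baseline are large or if utilities are more variable at 6 months.

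A reader might infer that the planned result would be biased, or that adjustment would make the QALY effect detectable. Neither follows. Both estimators centre on the truth under randomisation, and an adjusted SE of 0.0043 (SD 0.2, rho 0.5) still exceeds the illustrative direct gain of 0.0005 to 0.002. Adjustment removes avoidable noise, no more. It is a worthwhile correction, not one on which the trial's validity depends.

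**What to change.** In the Health economic evaluation section, state that incremental QALYs will be estimated as the arm coefficient from a regression of each woman's 6-month QALY on randomised group and baseline EQ-5D-5L utility. Use that estimate in the incremental cost per QALY and in its uncertainty analysis, and report unadjusted arm means descriptively. A random effect for practice, as in the clinical models, is optional and not needed for this point.

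The cost is one sentence, with no new data, visits or participants. Baseline utility is already needed to start the curve, so the covariate excludes no woman whose QALY could otherwise be calculated. If a fuller plan already specifies this, align the article's wording with it.
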